### Timeline

For this purpose, potential participants have a screening visit, where participants give written informed consent, blood and urine samples are collected and extensive patient history as well as questionnaires on PCOS symptoms, probiotic intake, depression symptoms and diet are collected. A soy challenge test as well as a functional gut permeability test are scheduled at home, requiring the participants to take urine and stool samples. For the soy challenge test, participants consume 2 × 250 ml soy drinks for two consecutive days, followed by urine sample collection at home each morning the day after soy consumption, similar to Setchell et al. [29]. In the morning of the second urine collection day, participants then drink a sucrose-mannitol-lactulose solution followed by 5 h of urine collection to measure gut permeability. Stool samples are collected before and after soy consumption.

At the first visit (taking place four weeks at the latest after the screening visit), participants deliver the collected stool and urine samples and receive a randomized package of intervention product, which they will take for the next six months. The probiotic and placebo arms get 200 sachets each respectively, to be taken once daily. The metformin group receives 400 tablets of 500 mg metformin, to be taken once daily for the first 7 days of intervention before increasing the dosage to twice daily.

Participants are asked to document any significant health changes or dietary intakes as well as the first day of each menstrual cycle. The intervention is scheduled to last 161 to 180 consecutive days, depending on the date of the second visit.

At the end of their intervention, they will repeat the isoflavone challenge and the functional gut permeability tests at home and deliver the respective samples to the outpatient clinic at their second visit (taking place 24–26 weeks after the first visit). There, the blood and urine tests from the screening visit will be repeated.

Participants in the blinded arms of the trial have the option to further take part in a follow-up period of an additional six months, during which they would take the probiotic formula (without placebo), followed by a follow-up visit scheduled one year after trial enrollment.

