### Intervention

#### Probiotic and placebo

The main intervention in this trial is a dietary food supplement powder containing seven probiotic bacterial strains: lactobacillus salivarius W57, lactobacillus casei W56, lactobacillus rhamnosus W71, lactococcus lactis W58, enterococcus faecium W54, lactobacillus plantarum W62 and lactobacillus acidophilus W22 (manufactured by Winclove Probiotics B.V., Netherlands; marketed as OMNi-BiOTiC® metabolic by Institut AllergoSan GmbH, Graz, Austria) In addition, the probiotic contains 2000 IU cholecalciferol. Other ingredients are corn starch, maltodextrin, fructo-oligosaccharides, galacto-oligosaccharides, polydextrose, plant proteins, potassium chloride, magnesium sulfate, manganese sulfate and lactose. By comparison, the placebo is very similar to the probiotic visually and in taste and smell. Its ingredients are corn starch, maltodextrin, potassium chloride, magnesium sulfate and manganese sulfate. Both Verum and Placebo are packaged in blank sachets, so that patients, caregivers, investigators and outcome assessors are blinded to their content.

On each sachet, the expiration date and the study acronym (ProPCO-RCT) is clearly shown. 50 sachets are packed in one box, where the instruction for ingestion, the expiration date, the randomization code and the ingredients are noted. The bacterial strains are mentioned on every box with the symbol +/- (regardless if the strains are included or not). Every participant receives 4 boxes, in total 200 sachets. An excess number of sachets (the intervention period is only 180 days) is included in case the participant loses a few.

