#### Secondary outcomes

Glucose metabolism via HOMA and Matsuda indices as determined through an oral glucose tolerance test.Other hormonal parameters of PCOS (Anti-Müllerian hormone; androstenedione; follicle-stimulating hormone FSH; luteinizing hormone LH; dehydroepiandrosterone-sulphate DHEA-S; 17α-hydroxy-progesterone; 17β-hydroxy-estradiole; total testosterone, 25-hydroxy-cholecalciferol).Hirsutism (modified Ferriman-Gallwey score).Body weight (body-mass-index BMI; waist-to-hip-ratio).Gut permeability and inflammation (functional sucrose-lactulose-mannitol test; surrogate parameters: serum diaminooxydase; stool zonulin; calprotectin; lipopolysaccharide; soluble cluster of differentiation sCD14; bacterial DNA).Gut lumen and mucosa microbiome composition (16 S-RNA gene sequencing).Phytoestrogen production -log10 (equol to daidzein concentration ratio in urine) obtained via the soy challenge test)Quality of life (PCOS questionnaire; depression questionnaires; diet questionnaires).

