#### Sample size calculation

Prior to this RCT, we conducted a short pilot trial with 30 women with PCOS (EC number 30–205 ex 17/18), randomly assigning 10 women into three probiotic intervention arms respectively, both to test our methodology as well as to assess the feasibility of improving PCOS symptoms with probiotics ([name], [name], [name], [name], 2020, data on file).

In the pilot study 10 participants received OMNi-BiOTiC® metabolic for 3 months and showed a median (minimum-maximum) reduction in free testosterone levels of -0.3 pg/ml (-1.7-2.5). We assumed that over 6 months the reduction in the probiotic group would be improved to -0.6 pg/ml, which corresponds to 20% of the free testosterone levels found in healthy women based on the cut-off value of 3,16 pg/ml free testosterone in our Endocrinology Lab platform. A sample size of 54 in each group would have 80% power to detect a difference in means of -0.6 pg/ml assuming that the common standard deviation was 1.1 pg/ml using a two group t-test with a 5% two-sided significance level. Including a 10% dropout, 60 participants per group had to be included. For the metformin group in the open part of the trial, 60 participants were recruited as well. Therefore, the total anticipated sample size was 180.

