#### Statistical analysis of outcomes

The analysis of the collected data in the study will be performed with SAS v9.4. The primary analysis will be performed on the intention-to-treat population. Details regarding the defined populations and the statistical analysis will be provided in the statistical analysis plan (SAP). The SAP will be prepared before unblinding the trial.

The analyses described below will be performed for the comparison of the probiotic and the placebo arms and the probiotic and the metformin arms, separately.

Demographic and baseline characteristics will be summarized and compared between the groups descriptively. The data will be presented as summary tables and, where appropriate, as plots. Continuous variables will be presented as means, standard deviation, median, minimum and maximum, for categorical data frequencies and relative frequencies will be used.

The primary outcome, changes in serum free testosterone concentration from baseline (screening visit) to 6 months (visit 2) will be compared between the probiotic and the placebo arms by analysis of covariance (ANCOVA) with serum free testosterone concentration at month 6 as dependent variable, and the baseline serum free testosterone concentration and treatment group as covariates. If the assumptions of the ANCOVA are not fulfilled, the changes in serum free testosterone concentration (i.e. difference visit 2 - baseline) will be compared between the groups by t-test or Mann-Whitney-U-test. A two-sided p-value of < 0.05 is considered to indicate statistical significance.

For the secondary and exploratory endpoints, group comparisons will be performed using parametric or nonparametric methods for unpaired data (as appropriate). I.e. the continuous secondary endpoints will be analysed similarly to the primary endpoint. In addition, linear mixed models will be used to analyse the group difference over the three time points (baseline, visit 2 and follow-up visit).

The collected stool samples will be sequenced with Illumina and the raw data will be uploaded on the Galaxy server of the Medical University of Graz. Microbiome analysis will be conducted using the QIIME 2 pipeline of the Galaxy server, the samples will be compared in respect to alpha- and beta-diversity using established methods. The results can be downloaded directly from the server.

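### End-of-intervention stool can contain the swallowed strains, so a 16S difference between arms cannot by itself be read as a change in the women's own gut microbiota

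*Protocol article*

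**What the plan says.** The product is "a dietary food supplement powder containing seven probiotic bacterial strains", taken once daily (Protocol article, Probiotic and placebo; Timeline). The placebo has none of these strains. It also lacks the fructo- and galacto-oligosaccharides, polydextrose, plant proteins, lactose and vitamin D that the probiotic contains.

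On timing: "The intervention is scheduled to last 161 to 180 consecutive days, depending on the date of the second visit" (Timeline). The home tests, which include stool collection, are repeated at the end of the intervention and the samples are handed in at visit 2. No interval off product is described. In the voluntary follow-up, women from both blinded arms take the probiotic, and the metformin arm has no follow-up.

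The secondary outcomes list "Gut lumen and mucosa microbiome composition (16 S-RNA gene sequencing" in brackets after the endpoint. The analysis text (Statistical analysis of outcomes) names the QIIME 2 pipeline and says that "the samples will be compared in respect to alpha- and beta-diversity using established methods". It names no metric and no step for the supplemented taxa, and leaves details to the SAP.

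**The concern.** 16S sequencing counts bacterial DNA in the sample and cannot tell whether a bacterium lives in the gut or was swallowed the day before. The probiotic arm receives seven strains by mouth and the other arms do not. Unless the analysis deals with this, the product's DNA counts as part of the woman's community in one arm only.

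The background section motivates the trial by reduced alpha diversity in PCOS. Added product taxa can raise observed richness with no resident change, so the artefact can point in the hoped-for direction. A positive result could then be reported as remodelling of the gut microbiota and linked to the hormone results. The exploratory probiotic-metformin comparison is exposed in the same way.

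**Working it through.** **Sample size, to fix n per arm.** Inputs from Sample size calculation: "A sample size of 54 in each group would have 80% power to detect a difference in means of -0.6 pg/ml". The planned SD is 1.1 pg/ml, and the test is an unpaired t-test at two-sided alpha 0.05. The normal approximation gives 2 × (1.96 + 0.84)² × 1.1² / 0.6² ≈ 52.8, so 53. The exact noncentral t calculation gives power 0.794 at 53 and 0.802 at 54, so 54 is right. "Including a 10% dropout, 60 participants per group had to be included": 54 / 0.9 = 60, also right. These figures serve the primary endpoint. The article gives none for the microbiome.

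**Is there an off-product sample after treatment?**
- Baseline stool is off product, but a change from baseline to visit 2 still includes product present at visit 2.
- Visit 2 stool comes at the end of intake. The Fig. 1 legend can be read as tests just after the last dose, but states no gap. Visit 2 is due 24–26 weeks after visit 1 (168–182 days) and intake lasts 161–180 days. The windows do not match exactly, so a gap of a few days cannot be excluded, but nothing presents one as a washout.
- At the follow-up visit, everyone who continued has been taking the probiotic.
- Mucosal biopsies come from about 10 women per arm at weeks 24–26, also with no stated washout.

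So no such sample is scheduled.

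**How far can product DNA alone move each metric?** Let s be the product's share of reads. The article gives neither s nor a bacterial dose, so s is varied. Assumed: 10,000 reads per sample, 150 resident taxa with the same distribution in both arms, four product features, and a background of 0.00001 of reads per product feature in all women.

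- *Presence/absence.* A feature with m expected reads is detected with probability about 1 − e^(−m). Background alone: m = 0.1, detection 10%. At s = 0.01%, one product read over four features gives m = 0.25 + 0.1 = 0.35, detection 30%. At s = 0.1%, m = 2.5 + 0.1 = 2.6, detection 93%. (This uses an even split and median values.)
- *Bray-Curtis.* Adding share s to one of two samples raises their distance by at most s × (1 − distance). That is at most 0.001 at s = 0.1% and 0.03 at s = 3%.
- *Shannon.* The index becomes (1 − s)H + s·Hp + h(s), with Hp the diversity within the product and h(s) = −s ln s − (1 − s) ln(1 − s). At s = 0.1%, h = 0.0079 and s·Hp is at most 0.001 × ln 4 = 0.0014, so the shift is at most 0.0093 − 0.001H. The terms have opposite signs and partly cancel.

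**Simulation.** 54 per arm, 150 replicates, no resident change. Mann-Whitney tests for Shannon and richness; PERMANOVA with 99 permutations for the two distances. Percentage of tests positive at 5%, by assumed median product share:

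| Metric | 0 | 0.01% | 0.1% | 0.5% | 1% | 3% | 10% |
|---|---|---|---|---|---|---|---|
| Shannon | 9 | 5 | 5 | 5 | 6 | 8 | 8 |
| Observed richness | 5 | 9 | 58 | 80 | 79 | 66 | 14 |
| Bray-Curtis | 8 | 4 | 5 | 13 | 26 | 99 | 100 |
| Jaccard | 7 | 67 | 100 | 100 | 100 | 100 | 100 |

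The Monte Carlo standard error is √(p(1 − p)/150): about 4 points at 50% and 2 at 5%. In the zero column the arms are identical, so its 5–9% shows the noise.

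**Other assumed inputs.** With 300 or 600 resident features, seven product features and 10% background detection, Jaccard PERMANOVA was positive in 5% or 4% of runs when detection in the probiotic arm was also 10%. It was positive in 59% or 37% at 30% detection, and in 100% at 50% or more. A further simulation gave, at a 0.1% share, Jaccard about 100%, richness about 70% and Bray-Curtis about 5%. Bray-Curtis reached 100% at 3%, and Shannon ranged from 4% to 32%. Removing the product taxa returned every test to about its nominal level.

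**The case against.** The strongest answer is that the article defers analysis detail to a SAP that is not shown. A filter may be there, and its absence here is not an error. That stands. What the SAP cannot change is the sampling: the protocol schedules no off-product stool after treatment.

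Second, the stated endpoint is microbial composition and diversity after intervention, not resident flora. An on-treatment comparison of the whole community is a valid randomised contrast. That also stands, and it is why the full-profile comparison should stay. It limits what a difference may be said to mean.

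Third, filtering has its own bias. It removes resident members of the same taxa and any true colonisation. Nor does it separate the bacteria from the oligosaccharides and polydextrose given only in the probiotic, which could themselves change resident flora. This is a reason for a sensitivity analysis and against making the filtered result the sole basis for every microbiome statement.

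A reader might infer that the microbiome test is bound to be positive simply because the product appears in stool. The documents do not support this. They give no bacterial dose, no stool abundance and no metric, and the results above run from nominal to 100% according to these. That women are still taking the product on the day of sampling is also an inference; sampling just after the last dose fits the text too.

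**Conclusion.** The concern holds as a limit on interpretation. A probiotic-placebo or probiotic-metformin difference in 16S composition can arise from product in transit and does not alone show a change in the women's own microbiota.

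Presence/absence beta-diversity is most exposed (67% positive at a 0.01% share, 100% from 0.1%), then observed richness (58–80% at 0.1–1%). Bray-Curtis is exposed only at larger shares (5–26% at 0.1–1%, 99% or more from 3%). Shannon is least affected: near nominal in the tabulated simulation, up to 32% under other inputs.

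All these rates rest on assumed read shares or detection rates, communities and sequencing depth. They show that the problem can be large, not how large it will be here. The endpoint is secondary, and the free testosterone analysis and its sample size are untouched.

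**What to change.** Keep the full-profile alpha- and beta-diversity comparison as planned. In the SAP, before unblinding:

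- Prespecify a sensitivity analysis that repeats these comparisons with the supplemented species or sequence variants removed (Lactobacillus salivarius, casei, rhamnosus, plantarum and acidophilus; Lactococcus lactis; Enterococcus faecium), for stool and for the mucosal biopsies.
- Remove them before samples are brought to a common depth. Otherwise, at a 10% product share, the probiotic arm would keep 10,000 × 0.9 = 9,000 resident reads against 10,000.
- Name the metrics.
- State that a change in the resident microbiota will be claimed only if the filtered analysis supports it.
- Report the product taxa separately as a marker of intake.

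The cost is one taxonomy filter in the planned QIIME 2 pipeline and a short SAP paragraph, with no new samples. The report should state the filter's limits: it loses resident members of the same taxa and any true colonisation, and it does not separate the strains from the other ingredients found only in the probiotic.

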### Adherence to study procedures

Due to stringent exclusion criteria and the long duration of the intervention period, we expect many participants to not be able to fully adhere to study procedures as outlined in the study protocol due to for example requiring antibiotic treatment or an unscheduled pregnancy. The study was planned and submitted prior to the COVID-19 pandemic outbreak, and therefore in many cases appointments and schedules for trial procedures may need to be altered. In such a case, deviations from the study protocol are documented in the CRF and participants may still continue with trial participantion. For the purposes of statistical analysis, all participants will be considered for the intention-to-treat analyses. The same statistical analyses will be applied additionally for the subpopulation that completely adhered to the trial protocol.

### Data collection and handling

For data collection, the newest version of SPSS (currently Version 26) will be used.

The results from the medical history and the physical examination are entered in the CRF. In addition, we will document the visit progress and whether every test and procedure was completed according to the protocol. This includes the laboratory codes used to identify the lab results, the intervention code from the sachets (or the allocation to metformin), as well as any adverse events.

For monitoring purposes, data from the paper CRF will be entered into an online CRF available at the Phoenix database of the Medical University of Graz.

The lab results from the study will be measured at the Endocrinology Lab Platform and the Clinical Institute of Medical and Chemical Laboratory Diagnostics and entered into the hospital patient information program “MEDOCS”, with the study-specific code attached to the data. From there, all results from the study can be downloaded in an excel sheet using the study code. Only authorized personnel have access to MEDOCS and only study-related personnel may access the study-specific results. All collected data will then be transferred to SAS for further analysis.

### Storage and data protection

This study adheres to legal regulations for the storage, registration, transfer and evaluation of data according to the Austrian Act on Pharmaceutical Products and data protection law (AMG). By signing the consent form, potential participants are informed and agree to the following:

Data obtained during the course of this clinical trial will be treated as strictly confidential, and passed on exclusively to the following persons without mentioning names (pseudonymised): the sponsor of the trial for scientific evaluation and assessment of adverse events as well as the biostatistician responsible for outcome assessment. Investigators responsible for the recruitment and data collection during the trial as well as the lab personnel responsible for outcome parameter measurements may work with personalized data (not pseudonymized) when required.

Monitoring and auditing personnel, employees of national and foreign health authorities as well as members of the competent ethics committee may also gain access to personal data at the study centre for auditing and quality control purposes.

The participant is entitled to terminate her participation in the clinical trial at any time without stating reasons and without future consequences or disadvantages. However, we are required by law to store and in individual cases inspect personal data even after trial dropout for a period of time as defined in the AMG.

### Data dissemination and publication

Any data obtained via this RCT may be published in conference papers, talks or posters, as well as peer-reviewed journals. This RCT is conducted as part of the PhD thesis of [name] and any data, figures and publications from this RCT may be used and cited in the doctoral thesis by [name].

Should any of the results from this study be considered for publication, the publication guidelines from the Medical University of Graz and the GCP guidelines must be followed. The decision to publish the results of the trial is made by [name], [name]. as the principal investigator and sponsor of the trial. Prior to publication, the respective materials are sent to the area leader at CBmed as well as a representative of Institut AllergoSan for approval and acknowledgment respectively.

## Data Availability

The datasets used and/or analysed during the current study are available from the corresponding author on reasonable request.
